### Missing data

2.15

Patients with at least one valid paired Anti-Xa and CT measurement will be included in the analysis (modified intention-to-observe population). Missing data will not be imputed. For repeated-measures models, maximum likelihood estimation will be used, which provides unbiased estimates under the assumption of missing at random. Sensitivity analyses will assess the impact of incomplete second measurements.

### Additional analyses

2.16

Dose–exposure–response relationships between administered anticoagulant dose, Anti-Xa activity, and VET parameters will be explored using linear mixed-effects models. Potential effect modification by patient-specific variables (e.g., age, sex, renal function, SOFA score, SAPS II) will be examined using interaction terms within the mixed-effects framework. No separate subgroup analyses are planned. Stratified analyses, if presented, will be considered descriptive. Exploratory analyses of clinical events (bleeding or thrombotic complications) will use logistic regression only if event numbers permit stable estimation. These analyses are considered hypothesis-generating.

## Discussion

3

Anti-Xa activity remains the reference standard for monitoring heparin therapy but provides only a narrow perspective on anticoagulant effect. In critically ill patients, fixed dosing frequently results in sub- or supratherapeutic levels, and Anti-Xa values correlate poorly with clinical outcomes. Moreover, logistical barriers and delayed turnaround limit its feasibility as a routine monitoring tool in intensive care. Global assays such as the VET offer broader functional evaluation by integrating plasmatic and cellular components of coagulation. Experimental and volunteer studies demonstrated strong correlations between the VET clotting time and heparin concentration, and modified assays achieved high classification accuracy for therapeutic ranges. However, clinical data are inconsistent: some reports failed to show correlations beyond peak levels or at prophylactic dosing, and sensitivity varied considerably across devices and reagents. Similarly, TGA has shown promise at therapeutic LMWH concentrations but lacks standardization and is less reliable at lower doses. These limitations are particularly relevant in critical illness. Septic patients exhibit profound, dynamically evolving disturbances of haemostasis driven by inflammation, endothelial dysfunction, altered antithrombin levels, and consumption or dysregulation of pro- and anticoagulant pathways. These mechanisms result in substantial variability in heparin pharmacokinetics and pharmacodynamics, making fixed-dose anticoagulation particularly unreliable. In a larger cohort of critically ill COVID-19 patients with repeated paired measurements, CT-RVV showed only a weak-to-moderate correlation with Anti-Xa, highlighting that CT-based detection may be strongly context-dependent (17). This underscores the need to identify biological and methodological modifiers (e.g., inflammation, AT levels, factor consumption) that may explain discordant profiles. Anti-Xa quantifies circulating heparin activity but does not capture the global coagulation phenotype characteristic of sepsis, including heightened thrombin generation, impaired fibrinolysis, or parallel bleeding risk. VET may better reflect this complex state by integrating cellular and plasmatic contributions to clot formation. Although, VET also has clinically relevant limitations in the ICU: sensitivity to platelet dysfunction and mild fibrinolysis is assay- and device-dependent, and acute-phase changes (e.g., elevated fibrinogen) can increase clot firmness and partially mask anticoagulant effects. Nevertheless, these results may better reflect the overall state of the patient’s coagulation system. Therefore, VET is interpreted as a functional whole-blood phenotype that may complement—but not universally replace—concentration-based Anti-Xa monitoring. Understanding the relationship between Anti-Xa, VET, and global haemostatic markers in septic patients is therefore essential to determine whether Anti-Xa alone is sufficient or whether functional assays can identify under- or over-anticoagulation earlier. Given the high incidence of thromboembolic and bleeding complications in sepsis, this study’s findings are expected to directly inform individualized anticoagulation strategies and support more reliable monitoring pathways in this high-risk population.

Sepsis, multi-organ failure, and endothelial dysfunction alter pharmacokinetics and pharmacodynamics, complicating both drug absorption and elimination. Consequently, Anti-Xa monitoring provides only a concentration-based readout and does not reflect the complex interplay between the procoagulant and anticoagulant pathways. In particular, it neglects the influence of elevated fibrinogen levels due to inflammation, increased platelet activation, and impaired fibrinolytic activity. Similarly, standard laboratory tests such as aPTT and INR are confounded by acute-phase reactants and inflammatory mediators. Additionally, Anti-Xa activity reflects heparin-dependent inhibition of a fixed amount of exogenous factor Xa and is therefore largely independent of endogenous factor X levels. In contrast, CT-RVV in whole blood may be influenced by variations in coagulation factor concentrations, including factors V and X. Such variability is considered part of the biological context of critical illness and is not treated as methodological noise but as a potential modifier of assay concordance. As a result, neither Anti-Xa nor conventional coagulation tests adequately capture the dynamic risk of bleeding and thrombosis in critically ill patients.

Point-of-care tests such as VET provide the practical advantage of immediate bedside results, potentially enabling timely adjustment of therapy. As has already been shown, VET can complement the monitoring of argatroban therapy and, in certain situations, may serve as the sole method, providing better performance than aPTT but without exceeding the accuracy of dTT (37). However, robust evidence on whether VET can substitute for or complement Anti-Xa monitoring in UFH and LMWH administration in critically ill patients is still lacking. Consequently, the clinical utility of these assays remains uncertain, particularly in sepsis and at prophylactic LMWH dosing, where therapeutic failure is frequently observed. The present study addresses these gaps by prospectively measuring Anti-Xa, VET, TGA, and extended haemostatic markers in critically ill patients treated with UFH or LMWH. By systematically evaluating correlations, dose–response relationships, and patient-specific modifiers, the trial aims to clarify whether VET clotting times in the RVV test can serve as surrogates for Anti-Xa. In addition, secondary analyses will assess whether VET or Anti-Xa aligns more closely with global haemostatic function, as defined by TGA variables, and whether TGA can help explain discordant results between concentration-based monitoring and functional assays. Ultimately, the results are expected to define the potential and limits of bedside viscoelastic monitoring and to guide patient-tailored anticoagulation strategies aimed at reducing both thrombotic and bleeding complications.

Several practical and operational considerations must be acknowledged when implementing the trial. First, patient recruitment in the ICU setting presents inherent challenges. The study population is characterized by acute illness, rapid clinical deterioration, and a frequent need for urgent interventions. These factors may complicate the timing of informed consent and sample collection and may limit the number of patients eligible for inclusion at predefined sampling points. The sample size was selected to allow estimation of the Anti-Xa–CT association under heterogeneous ICU conditions and to enable modelling of pre-specified effect modifiers. Nevertheless, subgroup analyses remain exploratory. Coordination with treating clinicians will therefore be essential to ensure both feasibility and minimal interference with clinical care. Second, laboratory logistics require careful planning. Anti-Xa assays and the advanced haemostatic variables utilized in this protocol are not available as POC tests and necessitate plasma preparation, specialized reagents, and centralized laboratory support. Turnaround times, sample transport, and pre-analytical variables (e.g., platelet factor 4 release, sample handling under emergency conditions) may affect the results. In contrast, VET devices provide real-time bedside results but require trained personnel, standardized procedures, and rigorous quality control to ensure reproducibility across time points and operators. Ensuring consistent calibration of instruments and adherence to testing protocols is therefore critical. Third, the study must account for the heterogeneity of critically ill patients. Pathophysiological differences, including sepsis, organ dysfunction, and variable pharmacokinetics of anticoagulants, may influence the comparability of the results. This variability is intrinsic to the research question, but it complicates data interpretation and increases the need for a sufficient sample size and stratified analyses to identify relevant subgroups. Fourth, operational constraints in integrating advanced haemostatic assays into routine workflows should be considered. Thrombin generation assays, while promising as global markers of coagulation, are technically demanding, require specialized laboratory infrastructure and are not standardized across platforms. These factors may limit their widespread adoption outside research settings, and interpretation of results must be made with caution.

Finally, ethical and organizational considerations are relevant. Many patients in the ICU lack the capacity to consent, necessitating surrogate decision-making or deferred consent procedures, which must comply with local regulations.

In summary, while this study is designed to answer important clinical questions, it faces challenges related to patient recruitment, laboratory logistics, assay standardization, and the complexity of critical illness. Addressing these operational aspects proactively will be essential for the successful conduct of the trial and for the generation of robust, generalizable results.

## Data management

4

### Documentation

4.1

All data collected during the study, including medical history, comorbidities, test results, and adverse events, will be recorded by authorized personnel. A special identification list will be maintained to ensure the identification of patients and participants after the study has been completed. If a participant withdraws consent, they will be removed from the identification list to ensure data privacy and confidentiality.

### Data collection

4.2

Patient data will be collected via the patient data management system of the intensive care unit of the study center. Data collection will be carried out in accordance with the established study methods, and all collected data will be treated in compliance with data protection regulations. Demographic and clinical variables, including sepsis scores and severity indices, will be documented pseudonymized in standardized case report forms (CRFs). Data collection will follow predefined protocols, and all assessors will be trained in study procedures to ensure reproducibility and data quality.

### Withdrawal of individual participants (dropout)

4.3

If the exclusion criteria are unknowingly met at the time of study enrolment, later exclusion may occur. Withdrawal of consent will result in the exclusion of the collected data. Published data are untraceable once published.

### Data privacy and confidentiality

4.4

Data are collected pseudonymously, meaning that identification can only occur via the identification list. The identification list linking study codes to personal identifiers will be stored separately and securely, accessible only to authorized study personnel. No names, initials, or directly identifying data will appear in the study database or publications. Participants can withdraw their consent at any time. The raw data will be stored for at least 10 years in accordance with the “Statute for Ensuring Good Scientific Practice” of the TUD Dresden, Dresden, Germany. All handling of personal data complies with the EU General Data Protection Regulation (GDPR) and institutional policies on data protection.

### Archiving of original data

4.5

The collected data are stored in an electronic database within the network of the University Hospital Dresden. The data were deleted no earlier than 10 years after the study’s conclusion.

### Access to data

4.6

The data collected as part of this study will be made available in anonymized form in the Open Access Repository and Archive for Research Data of Saxon Universities OPARA (38).

### Methods in analysis to handle protocol non-adherence and any statistical methods to handle missing data

4.7

As this is an observational study, no per-protocol versus intention-to-treat analysis distinction applies. The analysis population will include all patients with at least one valid paired measurement of Anti-Xa and VET (modified intention-to-observe). Patients who withdraw consent will be censored at their last available measurement. Missing data will be assessed for this mechanism. All patients with at least one valid measurement will be included in the analysis. For analysis of repeated measures, incomplete data points will be excluded pairwise in correlation analyses. For data considered missing at random, no data imputation is planned.

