### Thrombin generation

2.8

Thrombin generation will be measured using the Innovance® ETP assay (Siemens Healthineers, Marburg, Germany) on an automated coagulation analyser (BCS XP, Siemens Healthineers). Measurements will be performed in platelet-poor plasma. Coagulation will be initiated by addition of tissue factor and phospholipids in the presence of calcium according to manufacturer instructions. Thrombin formation will be quantified via cleavage of a chromogenic substrate, and the increase in optical signal over time will be recorded continuously. The assay software corrects for α2-macroglobulin–bound thrombin activity. From the resulting thrombin generation curve, the following parameters will be derived:

Endogenous thrombin potential (ETP; area under the curve)Peak thrombin generationLag time (time to initiation)Time to peak thrombin generation

Thrombin generation is included as a plasma-based global coagulation assay to complement whole-blood viscoelastic testing and Anti-Xa activity measurements. We acknowledge that PPP-based TGA differs from whole-blood clot dynamics and is sensitive to cellular effects; therefore, TGA results will be interpreted as a complementary plasma-based global readout rather than a direct proxy for whole-blood viscoelastic parameters.

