### Obtained laboratory and patient data

2.10

Primary outcome

1) Variable: VET CT in the RVV test (UFH/LMWH).Metric: Correlation with Anti-Xa activity (for UFH/LMWH); correlation coefficient (Spearman); multivariable mixed-effects regression to account for repeated measures.Aggregation: Point estimates with 95% CI.The time points are as follows: 4 h after the administration of LMWH (expected peak level) or steady-state sampling during continuous UFH infusion.Clinical relevance: Evaluates whether VET-CT can serve as a surrogate for Anti-Xa and assesses its potential as a surrogate monitoring tool.

Secondary outcomes

1) Variable: VET CT in the RVV test (UFH/LMWH); Anti-Xa activity.Metric: Correlation with TGA variables.Aggregation: Spearman correlation coefficients with 95% CIs and regression coefficients for adjusted analyses.Time point: As the primary outcome.Clinical relevance: Examines whether VET provide complementary or superior information to Anti-Xa activity for characterizing global haemostatic function.

Exploratory outcomes

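### If heparin leaves a sample with no thrombin-generation curve, the stated missing-data rules drop it from the lag-time and time-to-peak correlations only, and understate those two associations

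*Protocol article*

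**What the plan says.** Section 2.8 lists the readouts taken from each thrombin-generation curve: "Endogenous thrombin potential (ETP; area under the curve"), peak, lag time (the time until generation starts) and "Time to peak thrombin generation". Section 2.10 makes the correlation of CT-RVV and of Anti-Xa with these variables the secondary outcome, reported as "Spearman correlation coefficients with 95% CIs and regression coefficients for adjusted analyses". No single readout is given priority. Section 2.2 includes patients with prophylactic through to therapeutic targets. LMWH is sampled at the expected peak and UFH at steady state.

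Three statements govern a data point without a value:

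- Section 4.7: "incomplete data points will be excluded pairwise in correlation analyses".
- Section 2.15: "Missing data will not be imputed". The repeated-measures models rest on maximum likelihood, "which provides unbiased estimates under the assumption of missing at random".
- Section 4.7 again, with a condition that 2.15 lacks: "For data considered missing at random, no data imputation is planned". The sentence "Missing data will be assessed for this mechanism" also stands there, but nothing says what follows if the data are judged not missing at random.

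None of these separates a sample that was not taken, or that failed technically, from a sample whose result lies beyond what the assay can read.

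**The concern.** Lag time and time to peak are times to an event on the curve. If thrombin generation never starts, neither exists, while ETP (an area) and peak (a height) still have a value of about zero. The sample is therefore complete for two readouts and incomplete for the other two. Such samples would tend to be the most strongly anticoagulated, because the gap is produced by the very effect being correlated.

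Two things are at stake. The four readouts would be correlated on different sample sets, so their effect sizes would not be comparable. And the associations for lag time and time to peak would be pulled toward zero. The abstract expects discordance between Anti-Xa and global haemostatic markers in a relevant subset. A correlation weakened by deletion could be misread as part of that discordance.

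**Working it through.** The plan gives no figure on this point, so there is none to reproduce. The question is how far deletion moves the result.

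**Inputs from the protocol article.** 66 patients with two samples each, so up to 132 samples; ICC 0.3 and design effect 1.3 (section 2.12).

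**Assumptions.**
- The share f of samples with no curve is not given; 5% to 30% is used.
- The correlation between a marker and the latent lag time is not given; 0.6 is the main case. That is the plan's UFH planning value for Anti-Xa against CT, borrowed here, and not a thrombin-generation value. Values from 0.3 to 0.7 were also run.

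**Method.** Marker x and latent lag time y are bivariate normal with correlation r (400,000 draws). The top share f of y is marked as having no curve. Spearman is computed (a) with those samples kept at a tied longest rank and (b) after pairwise deletion. The least-squares slope of y on x after deletion is divided by the true slope r.

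| No-curve share | Kept, tied rank (r = 0.6) | Deleted (r = 0.6) | Difference | Slope / truth (r = 0.6) | Kept (r = 0.4) | Deleted (r = 0.4) |
|---|---|---|---|---|---|---|
| 0% | 0.580 | 0.580 | 0 | 1 | 0.383 | 0.383 |
| 5% | 0.580 | 0.544 | 0.036 | 0.87 | 0.382 | 0.351 |
| 10% | 0.579 | 0.517 | 0.062 | 0.80 | 0.382 | 0.330 |
| 20% | 0.574 | 0.475 | 0.099 | 0.69 | 0.378 | 0.301 |
| 30% | 0.565 | 0.441 | 0.124 | 0.60 | 0.371 | 0.277 |

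The tied rank loses almost nothing; deletion loses steadily more.

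**Source of the deletion.** If samples are removed on the marker instead of on lag time, Spearman at r = 0.6 is nearly the same (0.544, 0.517, 0.476, 0.441). The slope column does depend on removal by lag time itself. In that case the missingness depends on the unobserved outcome, so a likelihood model that assumes missing at random would not be expected to repair it.

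**At the planned size.** With 66 patients, two samples each and ICC 0.3, deletion leaves 125, 119, 106 and 92 of 132 pairs at the four shares. Deletion gives a weaker Spearman than the tied rank in about 96% to 97% of simulated trials at r = 0.6, and in 86% to 88% at r = 0.4.

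**Against sampling error.** Effective observations are 132 / 1.3 = 101.5. The approximate 95% half-width around 0.58 is (1 − 0.58²) × 1.96 / √(101.5 − 3) = 0.664 × 0.197 = 0.13. The shift at 5% to 10% is below half of that; at 30% it is close to the whole of it.

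**Ranking of two markers.** After 20% deletion, latent correlations of 0.3, 0.4, 0.5, 0.6 and 0.7 give Spearman 0.223, 0.301, 0.385, 0.475 and 0.579. All shrink and the order holds.

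**The case against.** The strongest reply is that the trigger is not in the documents. Nothing says that heparin abolishes thrombin generation in any sample, how often, or what the analyser then reports. The introduction speaks of good correlation with Anti-Xa at therapeutic LMWH doses and of reduced, not absent, thrombin generation. The discussion places the assay's weakness at lower doses. This stands: the size can only be shown as an assumed range, and it is zero if no such sample occurs or if the analyser returns a usable ceiling value.

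A second reply is that coding of out-of-range results belongs in the analysis plan, which is not shown. That would answer a plan that was silent. This one states a rule, and the rule as written covers such samples. The planned check of the missing-data mechanism is a partial safeguard, but no action is attached to it, and section 2.15 forbids imputation whatever the check shows.

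A third reply is that these analyses are modest in status. Section 2.14 makes simple correlations descriptive, and section 2.12 calls the thrombin-generation analyses hypothesis-generating, with no sample size of their own. This stands too and limits the weight of the point. Section 2.10 nevertheless reports regression coefficients for the same outcome, and these shrink as well.

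A reader might infer more than the documents support:

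- *That the secondary correlations as a whole are weakened.* ETP and peak keep every such sample if a flat curve is recorded as about zero.
- *That the comparison of CT-RVV with Anti-Xa is reversed.* Deletion on a thrombin-generation value removes the same samples from both comparisons, and the order was preserved in the calculation.
- *That the primary analysis suffers the same loss because some CT-RVV runs show no clot.* The documents give no run limit and no sign that this happens.

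**Conclusion.** The point holds in conditional form and is limited to lag time and time to peak. By the plan's own definitions, a curve that never starts has neither value, and the stated rules would remove the sample for a reason tied to the effect under study. For an assumed 5% to 30% of such samples and a borrowed latent r of 0.6, these associations are understated by 0.036 to 0.124 on the Spearman scale and by 13% to 40% on the slope. The slope figure further assumes that absence depends on lag time itself. The likely harm is a misreading of strength: two readouts that look discordant with heparin exposure partly because the most suppressed samples were dropped. This is an inexpensive improvement to a stated rule, not a threat to the main result.

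**What to change.** In sections 2.15 and 4.7:

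1. State that a sample with no thrombin-generation curve is a valid result beyond the readable range, not a missing value.
2. In Spearman analyses, give it the longest tied rank for lag time and time to peak.
3. Report the number of such samples by heparin type.
4. Reserve pairwise exclusion for samples not taken or technically failed.
5. Reconcile the unconditional no-imputation sentence in 2.15 with the conditional one in 4.7, and say what follows if the mechanism check points away from missing at random.

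The cost is a few lines of text. The rank rule needs no distributional assumption and changes nothing if no such sample occurs. It should be fixed before the data are seen, since it would be less credible afterwards. A right-censored regression can be added as an optional sensitivity analysis in R, which is already planned. Its downside is a distributional assumption and the need for a stated censoring limit, which the article does not give.
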